**Fig 1 pone.0298154.g001:**
[figure not shown]
Participating countries by income-level World Bank status June 2021.

Within each country, a lead clinician (CLC) was assigned to coordinate the national activity and secure approvals by local or national ethics committees as required. As an example, the protocol submitted in Kenya, is included as a S2 File. CLCs advised on the languages needed and provided contacts for translators who could meet the requirements of the various ethics committees. The survey has been translated into 28 languages using the agencies recommended by the CLCs, and translations checked by back translation where required by national ethics, the clinical team, the study team, and by one or two local patients. The CLC is responsible for the implementation of the protocol, choosing optimal methods of sample selection and data collection for their setting. The CLC is responsible for building their network of participating sites, each with a local site lead (LSL). Depending on the health infrastructure and resources available, countries may have between one and 12 sites, ideally representing the typical range of care women might receive within the country. This is summarised in Fig 2.

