### Sample selection

Initially the OC recommended a standardised single approach to sample selection, with all patients diagnosed within the last five years at a participating site being approached for inclusion in the study. This would have allowed for inclusion of survivors with a wide-spread time since diagnosis, and reached patients who might otherwise have stopped treatment or be in remission. However, given the diversity of resources, attendance patterns, and access to patient records between countries and even participating centres within a country, the OC decided a single approach was not feasible. A randomised approach was also not deemed suitable given the challenges ensuring consistency in implementation across many sites. Instead, a convenience sampling approach was approved, offering three different models listed below. To compensate for the variety of approaches, the method of sample selection will be recorded for each patient to allow for data stratification if required. CLCs suggest all participating centres in their country follow the same approach, but this is not mandated. The sample selection approaches, and associated caveats are as follows:

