The site team reviews all cases on their records that have been seen in the previous five years, with a view to contacting eligible ovarian cancer patients and inviting them to participate. This approach is dependent on availability of staff resource, accessible patient records and reliable communication methods with patients. It might also catch patients who have previously stopped treatment but may also require them to attend a new appointment if they cannot be reached by email, or WhatsApp, and so completion rates may be lower;The site team reviews all cases of ovarian cancer patients who have recently attended an appointment, working backwards in a sequential manner, until they meet the minimum or preferred sample size. This requires extra resource and good record-keeping, and may mean the sample selected is skewed to those with a more recent diagnosis; andThe site team reviews all cases of ovarian cancer patients due to attend a forthcoming appointment in person or virtually, inviting eligible patients to participate at that appointment. This approach requires less staff resources, as patient notes and attendance in clinic is already factored in. It may also improve completion rates. However, this approach may result in the inclusion of a greater proportion of patients with a more recent diagnosis, those on active treatment or experiencing complications, and can add time to clinic appointments.

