### Data collection procedure

The administrator generates a unique identifier number (UIN) for the ovarian cancer patients on REDCap and some basic demographic and clinical data is entered to determine eligibility (S6 File). This information includes age at diagnosis, month and year of diagnosis, type and stage of ovarian cancer and current treatment status. This provides an overview of women attending the clinics and allows basic comparisons between the groups who do and don’t consent.

Women with ovarian cancer are then approached and taken through an informed consent process. They are given written and verbal information about the study. If they are not attending clinics directly, they can be sent this information by email or be spoken to by phone. They are taken through the purpose and outline of the study and the risks and benefits of taking part are discussed. They are informed that they do not have to participate, they do not have to answer every question, and that they can withdraw their information up to 3 months after the close of data collection. They are then asked whether or not they consent to participate in the study and if they consent, whether they wish to i) self-complete a paper survey, ii) self-complete the survey via a secure email link, iii) self-complete the survey via a secure WhatsApp link (or other online messaging app), or iv) whether they wish to have the administrator ask them the questions. Their decision is recorded. Women who receive the information in person, or by phone need to record their consent in writing, and a copy is kept in a secure location on site. In addition to the standard consent form for the study, some local sites require patients to also complete their own informed consent forms, as part of the ethics approval. One country asked for women to consent with a thumbprint. Women who receive the information by email or WhatsApp can consent electronically at the start of the survey, or they can request an administrator contact them if they have questions before deciding.

Local teams are encouraged to supply the women with some written as well as verbal information about ovarian cancer, including at least two sources of potential support and information, be they non-governmental organisations (NGO), charities, or other groups (S6 File). The process is summarised in Fig 3.

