There are several limitations to the study. First, it will only capture experiences from women who have been able to afford or access a diagnosis and subsequent treatment. In some participating countries, there is just one centre that diagnoses and treats the condition so there are many economic, geographic, societal and cultural barriers preventing symptomatic women from getting medical help. Second, the varied approach of sample selection may naturally introduce biases, but it is not feasible to apply a uniform approach in all participating sites. To account for this, sensitivity analyses will be conducted by including and excluding certain selection methods where distinct patterns are observed. Third, the minimum sample size per country will only provide a broad overview with wide confidence intervals at a standalone country level. However, the regional and global analysis will be able to determine how a country differs from the others in the study with greater accuracy, helping focus priorities for action. Finally, by running the study through known contacts of the Coalition and IGCS, there may be biases in terms of women’s experiences, particularly around levels of care, as the CLC and LSL have access to training and networks of specialist clinicians.

The results of the study with analyses at global, regional, and thematic levels, will be disseminated through peer reviewed papers, with presentations at key relevant conferences. In this way it will contribute to the knowledge base on ovarian cancer globally, and in participating LMICs. It will be supported by a media outreach campaign. Each of the CLCs will be encouraged to submit papers for publication and presentations at national and regional level in local languages to extend the reach of the study and its findings. Subject to funding, the Coalition plans to work directly with some of the country teams to develop action plans and engagement with health policy makers, which will be informed by the study findings. Some of the participating countries plan to continue data collection, subject to the appropriate permissions, and/or adapt the study for other disease areas. By publishing the protocol, survey, and findings, the authors also hope to encourage other countries to consider running the study themselves.

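### Stratifying by, or excluding, selection methods cannot separate sampling bias from real country differences where a country uses one method; pre-specify adjustment for time since diagnosis

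*Protocol article*

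**What the plan says.** Sample selection explains that a single approach was judged infeasible and that "a convenience sampling approach was approved, offering three different models listed below". The models are a review of all records over five years, a backward review of recent attenders, and an invitation at forthcoming appointments. Study infrastructure makes the country lead clinician (CLC) responsible for "choosing optimal methods of sample selection and data collection for their setting". On uniformity, "CLCs suggest all participating centres in their country follow the same approach, but this is not mandated".

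Sample selection names the expected skews. The backward review, "working backwards in a sequential manner, until they meet the minimum or preferred sample size", may favour more recent diagnoses. Of forthcoming appointments it says that "this approach may result in the inclusion of a greater proportion of patients with a more recent diagnosis, those on active treatment or experiencing complications".

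Two remedies are stated. In Sample selection, "the method of sample selection will be recorded for each patient to allow for data stratification if required". In the Discussion, offered as the way to account for selection bias, "sensitivity analyses will be conducted by including and excluding certain selection methods where distinct patterns are observed".

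The screening data entered before consent include "month and year of diagnosis, type and stage of ovarian cancer and current treatment status" (Data collection procedure). Table 3 lists date of diagnosis as a possible confounder for two example outcomes, access to chemotherapy and access to cytoreductive surgery. Selection method is not listed for any outcome.

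**The concern.** Comparison between countries is the purpose of the study. The Aim states the hypothesis that key factors vary by country. Data analysis examines variation by country, region and socio-economic group and will identify outlying countries. Each country also receives a report that sets it against the average.

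If the method is chosen country by country, a difference produced by sampling has the same appearance as the difference the study is looking for. Outcomes that build up or fade after diagnosis, such as financial impact, support and information needs, or having had a genetic test, could then differ between two countries only because one sampled women sooner after diagnosis. A policy report could present that as a national problem. A larger pooled sample narrows the interval around such a difference but does not remove it.

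The trigger adds a second weakness. An analysis run only where a pattern is seen, or if required, is decided after the results are known.

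**Working it through.** **The plan's own figures.** With n0 = z² × 0.25 / e² and n = n0 / (1 + (n0 − 1)/N), taking z = 1.96 for 95% confidence and p = 0.5 (assumed, not stated):
- Global target: e = 0.025 gives n0 ≈ 1,536.6. With N = 823,000 (Introduction), n ≈ 1,533.7, rounded up to the stated 1,534.
- The 24 country minima in Table 2 (70 to 96) sum to the stated 2,160.

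**Can method be separated from country?** Put 24 country indicators and 2 method indicators (three methods, one as reference) into one model.
- If every country uses one method, the design matrix has rank 24 of 26. The method effects are not estimable.
- If even one country uses all three methods, the rank is 26 of 26. The method effect is then estimable, provided it is the same in every country.

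The documents do not give the mix of methods by country, so either case is possible.

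**What exclusion removes.** Assume one method per country and every country at its minimum. The women remaining are 2,160 less the minima of the k countries dropped, shown from the largest k minima to the smallest k:

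| Countries using the excluded method | Countries left | Women left |
|---|---|---|
| 4 | 20 | 1,778 to 1,861 |
| 6 | 18 | 1,588 to 1,689 |
| 8 | 16 | 1,398 to 1,508 |
| 12 | 12 | 1,022 to 1,138 |

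At k = 8 the total falls below 1,534. If methods are mixed within countries, exclusion thins countries instead of deleting them.

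**What a skew could do (all inputs assumed).** Suppose 30% of women under one year from diagnosis report an outcome and 50% of those later do, identically in two countries.
- Record-review country, 20% recent: 0.2 × 30 + 0.8 × 50 = 46%.
- Forthcoming-appointment country, 60% recent: 0.6 × 30 + 0.4 × 50 = 38%.
- False difference: 8 points.
- Both standardised to 40% recent: 0.4 × 30 + 0.6 × 50 = 42% in each, difference 0.

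With 90 women per country, the standard error of the difference is √(0.46 × 0.54/90 + 0.38 × 0.62/90) ≈ 0.073, so its 95% margin is about ±14 points. A two-sided 5% test then rejects with probability Φ(0.08/0.073 − 1.96) ≈ 19%, where 5% would be correct. For assumed shifts of 5, 10, 15 and 20 points around 50%, the probabilities are about 10%, 27%, 52% and 77%.

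**Does keeping one method settle it?** It removes differences between methods. It does not equalise time since diagnosis among countries sharing that method. The backward review stops at a sample-size quota, and the minima are 70 of 259 prevalent cases in Mozambique (27%) and 96 of 103,716 in India (0.09%). How far back each site would reach depends on its number of attenders, which the documents do not give, so this is a possibility and not an estimate.

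**The case against.** Several points on the other side stand.

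- A reader might infer that the include/exclude analysis is the only remedy. It is not: stratification is also stated, and it does permit comparison among countries that share a method. Each country's dataset is reviewed for local bias (Data management), and multivariable regression is planned.
- A reader might infer that method and country are one variable. The text says that uniformity is not mandated. There are 113 sites in 24 countries, with one to 12 per country, and Sample selection itself notes diversity between centres within a country. The loss of whole countries is therefore conditional.
- A reader might infer that excluding methods always leaves bias among the remaining countries. Restricting to a single method would remove the between-method part, at the cost of countries.
- The metrics named in the Data analysis text (stage, time to diagnosis, awareness) largely concern the period up to diagnosis and are less exposed.
- Table 3 is offered as examples, so its silence on other outcomes does not rule out adjustment. Full model specification is commonly left to a longer document.

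The last point does not dispose of the concern. The article does more than stay silent: it states a remedy and says that this accounts for the bias. In single-method countries the remedy cannot do so.

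**Conclusion.** The point holds in conditional form. Where countries follow the suggested single approach, neither stratification nor include/exclude analyses can distinguish a sampling effect from a country effect, and neither acts directly on the skew in time since diagnosis and treatment status that the protocol expects. The trigger is result-dependent in any case. The Discussion openly lists selection bias as a limitation; the fault is in the remedy chosen.

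The size cannot be derived from the documents. The 46% against 38% example rests entirely on assumed inputs. A reader might set its 8 points against the ±10 margin in Sample size, but that margin is for one country's proportion. The relevant margin for a difference between two countries of 90 women is about ±14 points. An 8-point bias would therefore not usually mislead a single comparison, although it raises the false-positive rate from 5% to about 19%. The concern applies to outcomes that can change after diagnosis, not to every key metric. The change is worth making because the needed variable is already collected.

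**What to change.** 1. For outcomes that can change with time since diagnosis (for example financial impact, information and support needs, access to genetic testing), pre-specify between-country comparisons adjusted for time since diagnosis by regression. Derive it from the recorded month and year of diagnosis and the date of survey completion. Report adjusted and crude results side by side, whatever pattern is seen.
2. Add current treatment status only as a sensitivity analysis, and only for outcomes that are not themselves about treatment. Treatment status may partly reflect access to care, which is one of the country differences under study.
3. Run the selection-method analyses regardless of the observed pattern. Estimate the method effect within countries that used more than one approach.
4. State beside each include/exclude result that it compares a different set of countries, and list them.

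The cost is analysis text only; no new data are needed. Intervals will be somewhat wider, and where a country has few women long after diagnosis the adjusted figure relies on the model. This is why regression is preferable to direct standardisation over many cells: three time bands by two treatment levels would average 70/6 ≈ 12 to 96/6 = 16 women per cell at the minimum sample sizes. Adjustment will not remove other selection, such as who can be reached, and the report should say so.

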## Introduction

### Global incidence and mortality

Ovarian cancer is the eighth most common cancer and eighth most common cause of cancer death in women worldwide [1]. GLOBOCAN estimates that in 2020 there were approximately 314,000 cases diagnosed, 207,000 deaths, and more than 823,000 women living within five years of their diagnosis. Women in low- and middle-income countries (LMICs) account for 70% of ovarian cancer cases [2]. A 42% increase in ovarian cancer incidence, and a 52% increase in mortality, has been predicted by 2040, with the greatest increase expected in LMICs driven by projected population increases [3, 4]. For example, Zambia is predicted to have an increase of 122% in ovarian cancer incidence and 132% in mortality. Further increases are expected linked to the changing prevalence of cancer risk factors, such as lack of physical activity, changing diets, additional body weight, and increasing urbanisation [5–8].

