### Sample size

The minimum sample size for each country is based on GLOBOCAN estimates of five-year disease prevalence in the country, producing results at the 95% confidence level (+/- 10%) [2]. CLCs can choose to recruit more patients to improve confidence intervals in their standalone results. In total, the study aims to collect data from at least 1534 women, which would provide results at a 95% confidence level, +/- 2.5%, based on global five-year prevalence. Should each of the 24 countries (3 low, 11 lower-middle and 10 upper-middle income countries) collect their minimum data, the sample size would be 2,160 (Table 2).

**Table 2 pone.0298154.t002:** Expected sample sizes by country and income level.

REGIONAL AREA	COUNTRY	WORLD BANK INCOME STATUS (JUNE 2021) [29]	MINIMUM SAMPLE SIZE	PREFERRED SAMPLE SIZE	FIVE-YEAR PREVALENCE OF OVARIAN CANCER
**Sub-Saharan Africa**	Ghana	Lower-middle	92	327	2190
	Kenya	Lower-middle	92	330	2314
	Malawi	Low	79	203	431
	Mozambique	Low	70	155	259
	Nigeria	Lower-middle	95	361	6079
	South Africa	Lower-middle	94	347	3559
	Uganda	Low	89	297	1242
	Zambia	Lower-middle	78	197	403
**North Africa**	Egypt	Lower-middle	95	364	6854
	Morocco	Lower-middle	93	340	395
**South-East Asia**	Malaysia	Upper-middle	94	357	4989
	Vietnam	Lower-middle	95	346	3468
**Western Asia**	Kazakhstan	Lower-middle	93	343	3207
	Uzbekistan	Lower-middle	92	322	1997
**Caribbean, Central, South America**	Argentina	Upper-middle	95	362	6192
	Brazil	Upper-middle	96	377	18912
	Colombia	Upper-middle	95	362	6344
	Guatemala	Upper-middle	83	236	604
	Jamaica	Upper-middle	72	165	290
	Mexico	Upper-middle	95	374	13529
	Peru	Upper-middle	93	345	3398
**South-central Asia**	Bangladesh	Lower-middle	95	364	7044
	India	Lower-middle	96	383	103716
	Nepal	Lower-middle	89	297	1297
Total		Lower-middle	2160	6815	198,713

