**Further analysis**		
**Outcome variables**	**Predictor variables**	**Possible confounders**
Access to chemotherapy	Age on diagnosis Family income Distance to hospital Who pays for ovarian cancer care Resource level of participating site	Stage of ovarian cancer Date of diagnosis Use of neoadjuvant chemotherapy
Access to optimal cytoreductive ovarian cancer	Age on diagnosis Family income Distance to hospital Who pays for ovarian cancer care Resource level of participating site	Date of diagnosis Use of neoadjuvant chemotherapy
Levels of awareness of ovarian cancer	Education level Family income level Distance to hospital Family history	
Time to seek help for symptoms	Age Education level Family income level Who pays for ovarian cancer care First person consulted re symptoms Number of visits prior to diagnosis Level of concern over symptoms Type of symptoms Number of symptoms	

We will perform descriptive and inferential statistics, overall and by country and economic grouping using statistical softwares such as STATA and R. Categorical variables will be summarised with counts and percentages, with Chi Squared Tests or Fisher’s Exact Test used to compare proportions between groups. Continuous variables, such as time to diagnosis, will be examined graphically and summarised using appropriate metrics (mean and standard deviation or median and interquartile range depending on the distribution of the variable data). Tests, such as Kruskal-Wallis, will be applied to continuous variables. Outlying countries will be identified and described.

Appropriate regression analysis approaches will be used to examine assocations between independent and outcome variables. Binary, ordinal or nominal regression will be used depending on the nature of the outcome variable. Univariable regression will be employed to examine individual associations and multivariable regression to examine combined assocations between predictor and outcome variables.

The two free-text answers will be translated, coded and analysed using qualitative content analysis to identify categories and possible themes.

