Each country will receive a bespoke report summarising their results, how these compare with the average for all participants at a global and/or regional level, and provide information about the context of ovarian cancer care in their country obtained through interviews and surveys with the CLCs. CLCs will ‘own’ the country specific data and will be encouraged to share their national findings, and utilise them for healthcare planning, further research and engagement activities in their country.

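### A country-versus-others difference is not more accurate than the country's own estimate, and the country reports use an average that contains the country being judged

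*Protocol article*

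**What the plan says.** The Sample size section sets each country's minimum for a 95% margin of ±10 points. It sets a global target of 1534 women, "which would provide results at a 95% confidence level, +/- 2.5%, based on global five-year prevalence". If all 24 countries "collect their minimum data, the sample size would be 2,160".

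The limitations paragraph of the Discussion admits that the country minimums give imprecise national results. It then turns, with a contrasting However, to the statement that "the regional and global analysis will be able to determine how a country differs from the others in the study with greater accuracy", and adds that this will help set priorities.

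The last paragraph of Data analysis (Methods) says that each country's report will summarise its results and "how these compare with the average for all participants at a global and/or regional level". The same section says "Outlying countries will be identified and described". The methods it names are chi-squared, Fisher and Kruskal-Wallis tests, and univariable and multivariable regression. It names no model that pools information across countries and no comparison that leaves the country out of its own benchmark.

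**The concern.** The Discussion offers the regional and global comparison as relief from wide national intervals. Pooling the other countries makes the benchmark precise, but it does nothing for the error from the 70 to 96 women in the country being compared. That error enters the difference in full.

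The comparator raises a separate problem. An average over all participants includes the country's own women, so part of the country is compared with itself. In a large pool this hardly matters. Table 2, however, lists three areas with two countries each (North Africa, South-East Asia, Western Asia), and there about half of the regional average is the country in question.

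The Aim section's hypothesis is that key factors vary by country, and the reports are meant to support national planning and approaches to governments. Readers would be told that the comparisons are more precise than they are and, in small regions, would see gaps much smaller than the real ones.

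**Working it through.** **Inputs.** Country minimums and preferred sizes come from Table 2, and the total of 2160 from Sample size. Global prevalence is from the Introduction: "more than 823,000 women living within five years of their diagnosis". The article does not state a planning proportion; p = 0.5 is assumed.

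**Reproducing the plan's figures.** With n0 = 1.96² × 0.25 / e² and n = n0 / (1 + (n0 − 1)/N):

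- Global: e = 0.025 and N = 823,000 give n = 1533.8, which matches 1534.
- Countries: e = 0.10 gives the printed minimum to within one woman for 22 countries. Vietnam comes to 93.5 against 95. Morocco's printed prevalence of 395 gives 77, not 93.
- The minimum column sums to 2160.

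The sizes are therefore single-proportion calculations. None of them is for a difference between countries.

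**Precision of a difference.** Var(country − others) = Var(country) + Var(others). The 95% margin is 1.96 × √[0.25 × (1/n_country + 1/n_others)], without finite population correction.

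- Egypt alone: 1.96 × √(0.25/95) = 10.1 points.
- Egypt against the other 2065 women: 1.96 × √[0.25 × (1/95 + 1/2065)] = 10.3.
- Egypt against Morocco, its only regional partner: 1.96 × √[0.25 × (1/95 + 1/93)] = 14.3, about 41% wider than Egypt alone.

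| Comparison at minimum samples | Margin of the difference | Country alone |
|---|---|---|
| Against all other countries | 10.2 to 11.9 | 10.0 to 11.7 |
| Egypt / Morocco | 14.3 | 10.1 / 10.2 |
| Malaysia / Vietnam | 14.3 | 10.1 / 10.1 |
| Kazakhstan / Uzbekistan | 14.4 | 10.2 / 10.2 |
| Rest of region, other three regions | 10.8 to 12.6 | 10.0 to 11.7 |

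**Dilution from including the country.** Let w be the country's share of the pool. Then country − average = (1 − w) × (country − rest).

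- Egypt, regional: 1 − w = 93/188 = 49.5%.
- Example: with true values of 60% in Egypt and 40% in Morocco, the regional average is (95 × 0.60 + 93 × 0.40)/188 = 50.1%. The reports show +9.9 and −10.1 for a 20-point gap.
- All six countries in two-country regions: 49.5% to 50.5%.
- South-central Asia (96 + 95 + 89 = 280): 184/280 = 66% to 191/280 = 68%.
- Sub-Saharan Africa and the Caribbean, Central and South America: 85% to 90%.
- Global: 2064/2160 = 96% to 2090/2160 = 97%.
- Unequal recruitment: if Egypt reaches its preferred 364 and Morocco its minimum 93, Egypt shows 93/457 = 20% of the gap and Morocco 364/457 = 80%.

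**Effect on a test.** The standard error shrinks by the same factor: Egypt's margin against the regional average is 0.495 × 14.3 = 7.1. The ratio of difference to standard error is unchanged. The narrower interval belongs to a smaller quantity and holds no extra information.

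**The case against.** The strongest defence is that greater accuracy could mean something other than a comparison with the standalone interval. Comparing a country with a large pool is more precise than comparing it with one other country: about ±10.3 points, against 1.96 × √(0.25 × 2/95) = ±14.2 for two countries of 95. This is true globally and in the larger regions. It fails in two-country regions, where the rest of the region is one country, and it is not the contrast that the sentence draws.

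A second defence is that regression is left open, and a partial-pooling model could improve country estimates. That stands as a possibility, so one should not infer that no global analysis could ever help. But the article names no such model, and the sentence presents the gain as already available.

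Third, benchmarking against an overall average is ordinary descriptive practice, and the article allows global and/or regional comparators. If regions were continents, Egypt would be 95 of 877 women in Africa and would keep 782/877 = 89% of the gap. This limits the halving to reports that use the regional comparator with Table 2's areas.

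Fourth, the protocol's own sizes use a finite population correction, which brings the small countries' standalone margins to about 10.0. The ordering survives: two margins of 10.0 combine to √(10.0² + 10.0²) = 14.1.

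Finally, the Discussion already warns of imprecision at country level. It does, but the disputed sentence then offsets that warning.

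**Conclusion.** The statement about accuracy is wrong for the analyses described. A country-minus-others difference is never more precise than the country's own estimate. The loss is slight against all other countries and about 41% in two-country regions. The comparator in the reports understates the displayed regional gap by about half for 6 of 24 countries at minimum samples, by about a third in South-central Asia, by 10–15% in the larger regions and by 3–4% globally. In two-country regions the share shown runs from about 20% to 80% if one country recruits its preferred size and the other its minimum.

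These figures assume p = 0.5, simple random sampling, no finite population correction, averages taken over participants and, for the regional figures, Table 2's areas.

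A reader might go further in three ways that the documents do not support:

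- **That the reports' comparator invalidates significance tests.** It does not, because the difference and its standard error shrink together.
- **That ±10 to 12 points is a floor for country comparisons.** Under simple random sampling, p = 0.5 at minimum n gives the widest margin. Egypt at 364 against 2065 others would have 1.96 × √[0.25 × (1/364 + 1/2065)] = ±5.6.
- **That a countable number of countries will be labelled outlying by chance.** The article states no rule for identifying them, so no such count can be derived.

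**What to change.** Delete the sentence in the Discussion, or reword it to say that country-versus-others differences are at least as uncertain as the country's own estimate. Suitable figures are up to about ±12 points against all other countries and about ±14 in two-country regions, at minimum samples and p = 0.5.

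In the country reports, compare each country with the other countries in the study or region, leaving the country out of its own benchmark, and show the 95% interval for that difference.

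The cost is one sentence and a change to the report template; no new data are needed. Equal weighting of countries and a partial-pooling model are optional choices on which statisticians may differ, and neither is needed to correct the point.
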